#### Position of chest wall tract metastases

Position of the central point of a chest wall tract metastases in relation to the reconstructed radiotherapy treatment field will be recorded as in field/out-of field recurrence. Where the central point falls on the edge of the radiotherapy treatment field this will be recoded as in-field recurrence

#### Pain scores

Patients will be analysed using the intent-to-treat method. All tests will be two-sided and a p value of 0.05 or less will be considered statistically significant. In patients who develop tract metastasis, the VAS pain score from the assessment immediately before the occurrence of the tract metastasis will be considered baseline. Descriptive analysis will be performed to summarise change in pain score from baseline to subsequent pain score. Two-sample t tests will be used to explore difference between treatments. A 20% increase in VAS pain score is considered significant. The proportion of significant increases in pain in both arms will be analysed using a two-sided χ^2^ test.

No formal interim analysis is planned.

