### Outpatient visits

The patient is reviewed in clinic 6, 12, 26 and 52 weeks following randomisation to assess for any signs of chest wall metastasis and to record any treatment-related toxicities. In addition, telephone follow-up at 4-weekly intervals following randomisation will determine if the patient has noted any chest wall nodules. If a patient is suspicious that a nodule has appeared, they will be invited to clinic for assessment.

If a chest wall metastases is confirmed, the position of the metastases is recorded in relation to the reconstructed radiotherapy treatment field.

Patients are asked to complete a visual analogue score (VAS) for pain at baseline, and at each telephone and clinic follow-up. Patients are specifically asked to only consider pain at the original site of chest wall intervention. If the patient develops chest wall nodules they will be asked to complete a VAS for pain at the site of the chest wall intervention at for the three nodules closest to the original intervention.

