### Outcome measures

The primary end point is the incidence of chest wall tract metastasis 6 months from randomisation. If a patient raises suspicion that a chest wall nodule had developed at telephone follow-up, they will be invited to attend an outpatient appointment with the investigator. If there is clinical evidence of a chest wall metastases, a chest wall metastasis cardio respiratory fitness (CRF) is completed using the clinic date as date of chest wall metastasis.

The secondary end points are:
Time from randomisation to chest wall tract metastasis (recorded on chest wall metastasis CRF)Position of chest wall tract metastasis recurrence in relation to radiotherapy field in patients randomised to experimental arm (in field/out-of-field, recorded on chest wall metastasis CRF)Acute and late skin radiotherapy toxicity (recorded by CTCAE v4.0 at baseline and at each outpatient visit on CRF)Pain from chest wall tract metastasis (recorded by VAS pain scores recorded on chest wall metastasis CRF)

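### For nodules first reported by telephone, the pain baseline is a score taken when the nodule was already suspected, and the 20% pain rule does not say what it is 20% of

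*Protocol article*

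**What the plan says.** Four statements in the Protocol article bear on the point.

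- **When pain is scored** (Outpatient visits): "Patients are asked to complete a visual analogue score (VAS) for pain at baseline, and at each telephone and clinic follow-up". Calls are 4-weekly. For clinics, "The patient is reviewed in clinic 6, 12, 26 and 52 weeks following randomisation".
- **How a telephone report is handled** (Outcome measures): "If a patient raises suspicion that a chest wall nodule had developed at telephone follow-up, they will be invited to attend an outpatient appointment".
- **How the event is dated** (Outcome measures): if the clinic finds evidence of a metastasis, the form "is completed using the clinic date as date of chest wall metastasis".
- **How pain is analysed** (Pain scores): in patients with a tract metastasis, "the VAS pain score from the assessment immediately before the occurrence of the tract metastasis will be considered baseline". Change from that baseline to a later score is summarised and explored with t tests. For the responder analysis, "A 20% increase in VAS pain score is considered significant", and the proportions in the two arms are compared with a chi-square test.

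The Introduction makes whether chest wall metastases cause symptoms the second of its two reasons for running the trial.

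**The concern.** A baseline for pain from a nodule should come from before the nodule was known. Here the event date is the confirming visit, while the baseline is whichever assessment comes just before it. For a nodule reported by telephone, that is ordinarily the reporting call. Pain the nodule already causes is then subtracted from every later score.

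The question at stake is whether nodules hurt, which the article uses to judge whether PIT, if effective, is clinically worthwhile. A baseline that absorbs nodule pain pushes the answer towards no increase.

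The responder rule adds a separate difficulty. A 20% increase can mean 20% of the patient's own score or 20% of the scale, and the two classify patients differently.

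**Working it through.** The article gives no computed figure for the pain analysis, so there is none to reproduce. The check follows the rules through for one patient, then looks at the threshold.

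**1. Sequence for a telephone-reported nodule.**
- Last contact before suspicion: VAS = P.
- Call at which the patient reports a suspected nodule: VAS = C (a VAS is taken at each call).
- Invited clinic visit confirms the nodule: this is the event date.
- Any later score used for the change: S.

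The assessment just before the event date is the call, so the baseline is C.

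**2. Size per patient.** The change under the article's rule is S − C. The change from before suspicion is S − P. The difference is (S − P) − (S − C) = C − P, whatever S is. Later worsening therefore still counts, but the pain already present at the call is lost. If C = P nothing is lost.

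**3. Illustration** (assumed scores on an assumed 0–100 scale: P = 10, C = 30, S = 32).
- From the call: 32 − 30 = 2 points; 2/30 = 6.7%. Not a responder on either reading of 20%.
- From before suspicion: 32 − 10 = 22 points; 22/10 = 220%. A responder on both readings.

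**4. Nodules first found at a routine clinic.** The preceding VAS was taken before detection, so the defect does not arise in this form, although that score need not precede biological onset.

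**5. How often the telephone route could apply.** The article does not say. As an illustration only, assume uniform onset and detection at the next scheduled contact. To week 26, calls fall at weeks 4, 8, 12, 16, 20 and 24, and clinics at 6, 12 and 26.
- A call comes next for 4 + 2 + 4 + 4 + 4 = 18 of 26 weeks (69%).
- A clinic comes next for 2 + 2 = 4 weeks (15%).
- Both fall in the same week for 4 weeks (15%).

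To week 52 the counts are 40, 4 and 8 of 52 weeks (77%, 8%, 15%). On these assumptions the route is not a rare one.

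**6. The 20% rule** (0–100 scale assumed).
- Relative: 0 × 1.2 = 0, so a percentage change from 0 is undefined. At 5 the target is 6, a 1-point rise; at 10 it is 12. At 60 it is 72, so a rise to 71 fails. Above 100/1.2 = 83.3 it cannot be met.
- Absolute: 20 points from any start, including 0. Above 80 it cannot be met.

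**7. How few patients decide the test.** With the planned 15% and 5% incidence (Sample size calculation), 280/2 = 140 per arm gives 21 v 7 patients with nodules. Applying the rates to all 374/2 = 187 per arm gives about 28 v 9. One reclassified patient moves the responder proportion by 1/7 = 14 or 1/9 = 11 percentage points in the PIT arm, and by 1/21 = 5 or 1/28 = 4 in the control arm.

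**The case against.** The strongest reply has five parts.

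- **The article may mean onset, not the clinic date.** The word used for the event in Pain scores could be read that way. However, the article defines no onset date; the only date it assigns is that of the clinic visit. On the onset reading the rule cannot be applied as written.
- **Later pain is still measured.** This stands. The later score is not limited to the confirming visit, and VAS collection continues at every contact. A reader might infer that the change spans only the days from call to clinic; the text does not say that.
- **Direct evidence on nodule pain exists.** This stands. Patients with nodules also score pain for up to three nodules nearest the intervention site (Outpatient visits), on a page added by amendment (Protocol and protocol amendments). Those scores need no baseline. Only the change and responder analyses are affected.
- **The threshold may already be absolute.** This stands as far as it goes. The failure at low scores belongs to the relative reading, which is the natural one but is not stated. What can be held against the text is that it leaves the choice open.
- **Such detail belongs in an analysis plan that is not shown.** This is fair for zero scores and visit windows. It does not answer the baseline point, because the article itself fixes a baseline rule and that rule gives the wrong score for telephone-reported nodules.

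**Conclusion.** The point holds for nodules first reported by telephone. For them the stated baseline comes from a contact at which the nodule was already suspected, and the change is understated by C − P. The direction is towards no increase wherever pain had risen by the call. The total effect depends on the share of nodules reported by telephone and on the mean of C − P, neither of which is given.

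Three stronger readings are tempting but not supported:

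- **That most nodules are affected.** The 69% and 77% above rest on assumed uniform onset and detection at the next contact. A call depends on the patient noticing the nodule, whereas the clinics look for signs of it.
- **That the measured rise shrinks by exactly the telephone share, or that the trial would find nodules painless.** This needs all nodule pain to be present at the call with no later rise, and it ignores the nodule-level scores.
- **That trivial rises at low scores dominate the responder proportion.** The article gives no distribution of scores.

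The 20% rule is ambiguous, and on the relative reading it behaves badly at low scores. Both matters concern a secondary endpoint, but one that the Introduction ties to the clinical meaning of the primary result. They should be settled before analysis.

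**What to change.** **Baseline.** Define it as the last VAS before the contact, telephone or clinic, at which the nodule was first suspected or found. Use the randomisation VAS as a sensitivity analysis rather than the main baseline. Radiotherapy must be able to start within 42 days of the most recent intervention (Inclusion criteria), so the randomisation score may include procedural pain.

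**Threshold.** State that the increase is an absolute change of 20% of the VAS range, applied to all patients including those starting at 0. Note that patients whose baseline lies in the top 20% of the range cannot meet it, and report how many there are.

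**Cost.** Wording only. Serial scores are already collected at baseline and at every contact. The rule does need the contact of first suspicion to be identifiable in the trial data. The small downside is a baseline score that is slightly older.

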Currently in the UK the routine use of PIT in patients with MPM depends on locality. A 2008 UK survey showed that 75% of radiotherapy centres are routinely using PIT.^17^ In addition, the small number of patients recruited to each arm, the high death rates, and overestimation of the rate of chest wall metastasis in the control arms, question whether the three previous randomised controlled trials were adequately powered. Furthermore, recent evidence shows that portal tracts are not always perpendicular to the skin^25^ and thus the small radiation fields centred on the chest wall scar employed by the previous negative studies may have been suboptimal.

There is now strong evidence to support the role of palliative chemotherapy in patients with MPM^26^ which is approved in the UK by the National Institute of Clinical Excellence (NICE).^27^ Importantly, the previous studies were conducted before palliative chemotherapy was widely used in MPM. Therefore, the role of PIT in the era of effective palliative chemotherapy remains undefined. In addition, no previous studies have used validated pain scoring tools to assess pain from tract metastases.

We believe a trial is essential for the following reasons: first an adequately powered RCT employing radiotherapy techniques ensuring adequate coverage of the entire portal tract will establish whether PIT should be offered routinely to patients with MPM after chest wall intervention in the era of palliative chemotherapy; second to establish whether chest wall metastases are symptomatic and thus, whether PIT, if effective, is clinically significant.

The hypothesis for this trial is that prophylactic irradiation of tracts will reduce the incidence of chest wall nodules from 15% to 5%. The primary objective of the PIT study is to determine the efficacy, as assessed by the incidence of chest wall metastasis, of prophylactic irradiation of tracts following invasive chest wall intervention in malignant pleural mesothelioma compared to no prophylactic radiotherapy. Secondary objectives include: the description of the toxicity of PIT; time from randomisation to chest wall tract metastasis in patients undergoing PIT compared with the no prophylactic radiotherapy; the assessment of pain from chest wall metastasis.

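### The between-arm t test on pain is confined to patients who develop a nodule, the outcome PIT is meant to prevent; the main pain comparison should cover all randomised patients

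*Protocol article*

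**What the plan says.** Under Pain scores, the protocol article first names the analysis principle: "Patients will be analysed using the intent-to-treat method". It then defines the starting point for the change score: "In patients who develop tract metastasis, the VAS pain score from the assessment immediately before the occurrence of the tract metastasis will be considered baseline". No baseline or change is defined there for anyone else. Three sentences build on it:

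- the test of mean change: "Two-sample t tests will be used to explore difference between treatments";
- the threshold for an important rise: "A 20% increase in VAS pain score is considered significant";
- the test of that rise: "The proportion of significant increases in pain in both arms will be analysed using a two-sided χ^2^ test".

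The Outcome measures section describes the endpoint in matching terms: "Pain from chest wall tract metastasis (recorded by VAS pain scores recorded on chest wall metastasis CRF". That form is filled in when there is clinical evidence of a chest wall metastasis.

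Data collection is wider than the analysis. Under Outpatient visits: "Patients are asked to complete a visual analogue score (VAS) for pain at baseline, and at each telephone and clinic follow-up". Those scores refer to the intervention site and come from every patient, with or without a nodule.

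The Introduction gives the reason for measuring pain as the trial's second purpose: "to establish whether chest wall metastases are symptomatic and thus, whether PIT, if effective, is clinically significant".

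**The concern.** Whether a patient has a nodule is the primary outcome, and the trial is built on the expectation that PIT changes it. A comparison of arms among nodule patients only is therefore a comparison of two groups formed after randomisation by an effect of treatment, and randomisation no longer protects it. The baseline is also post-randomisation, since it is the last score before the nodule appeared.

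Two consequences follow. A patient whose painful nodule was prevented contributes nothing to the t test, so benefit by prevention cannot appear in it. And if the nodules that still occur under PIT differ in kind from those in the control arm, the t test picks up that difference in mix and may lean either way.

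At stake is a p-value, judged at 0.05, that would be read as the trial's evidence on whether PIT spares patients pain.

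**Working it through.** **Inputs.** Nodule rates 15% (control) and 5% (PIT), two-sided 5% level, 80% power, 280 patients, 25% not surviving 6 months and 374 in total come from Sample size calculation. The 1:1 allocation comes from Trial design, so 187 per arm are randomised and 140 per arm are expected to survive 6 months.

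**The plan's own figure.** For two proportions with pooled variance under the null,

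n per arm = [1.96·√(2·0.10·0.90) + 0.8416·√(0.15·0.85 + 0.05·0.95)]² / 0.10² = (0.8316 + 0.3521)² / 0.01 = 140.1.

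Rounded up this is 141 per arm, or 282 (stated: 280). Then 280 / 0.75 = 373.3, or 374 in whole pairs, as stated. The design figures reproduce.

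**Who enters the t test.** Applying the design rates:

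| Base per arm | Control, 15% | PIT, 5% | Total |
|---|---|---|---|
| 187 (all randomised) | 28.05 | 9.35 | 37.4 of 374 |
| 140 (6-month survivors) | 21 | 7 | 28 of 280 |

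By the normal approximation, the difference detectable with 80% power is (1.96 + 0.8416)·√(1/28.05 + 1/9.35) = 1.06 SD. With 21 against 7 it is 1.22 SD. The exact t test gives 1.10 and 1.27 SD.

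**What the subgroup comparison estimates.** Let q be the share of nodules that are painful, the same in both arms. The documents give no value, so q = 0.3 to 0.7 is an assumption. Among nodule patients the comparison is q against q, a difference of zero for any q. The same holds for mean change if pain per nodule is unaffected. Over all randomised patients it is 0.15q against 0.05q. Power with 187 per arm is Φ{[|p₁−p₂|·√187 − 1.96·√(2p̄(1−p̄))] / √(p₁(1−p₁)+p₂(1−p₂))}:

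| q (assumed) | Nodule patients only | All randomised | Power, 187 per arm |
|---|---|---|---|
| 0.3 | 30% v 30% | 4.5% v 1.5% | 40% |
| 0.5 | 50% v 50% | 7.5% v 2.5% | 60% |
| 0.7 | 70% v 70% | 10.5% v 3.5% | 76% |

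**If the remaining nodules differ in kind.** Take 14 of 28.05 control nodules as painful (assumption).

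- If PIT prevents mainly painless nodules and leaves 9 painful among 9.35, the subgroup shows 96% v 50% against PIT. Over all randomised patients, painful nodules still fall from 14/187 = 7.5% to 9/187 = 4.8%.
- If PIT prevents all the painful ones, the subgroup shows 0% v 50% in its favour.

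The subgroup result depends on which nodules remain, and its sign need not match the effect on patients.

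**Mean VAS over everyone.** At the design rates, 10 percentage points more control than PIT patients have a nodule. If a nodule raises VAS by 1 SD (assumption), the all-randomised mean difference is 0.10 × 1 = 0.10 SD. Power is Φ(0.10·√(187/2) − 1.96) = Φ(−0.99), about 16%.

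**The case against.** Four points can be made for the plan.

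- *The chi-squared test may already cover everyone.* Its sentence speaks of both arms and gives no denominator. If patients without a nodule count as having no increase, it is an all-randomised comparison. This stands: that the chi-squared test is restricted to the subgroup is an inference. It does not rescue the t test, because a change score is defined only for nodule patients and the endpoint comes from the nodule form. If other patients were meant to use their entry score, the choice of baseline would itself depend on a post-randomisation event.
- *Intention to treat may only mean analysis by allocated arm.* On that meaning the label is incomplete rather than false. It still tells a reader that the comparison keeps the protection of randomisation, which the t test does not.
- *The stated aim needs no between-arm pain test.* The Introduction lists assessment of nodule pain as an objective without a comparison, unlike time to metastasis. The primary endpoint shows whether PIT prevents nodules, and the descriptive pain summary shows whether nodules hurt. This stands in part. A reader might infer that the trial cannot show whether PIT spares patients pain, or that such a benefit would be invisible; the documents do not support that. The fault lies in the between-arm test.
- *Pain is secondary and the t test exploratory.* True, and the primary analysis is unaffected. But the section also attaches a 0.05 significance rule to its tests.

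A reader might also set the 1.10 SD detectable among nodule patients against the 0.29 SD detectable with 187 per arm and infer a large gain in power. That does not follow. The first is a difference among nodule patients, the second a difference in mean VAS over everyone, most of whom have no nodule. To produce 0.29 SD overall, each nodule would have to raise VAS by about 0.29 / 0.10 = 2.9 SD.

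**Conclusion.** The concern holds for the t test and, conditionally, for the chi-squared test. At the design rates the t test compares about 28 control with 9 PIT patients (21 with 7 on 140 per arm), chosen by an outcome of treatment. If PIT works purely by preventing nodules, the expected result is no difference while painful nodules fall by two thirds. That follows from the structure and needs no value for the share of nodules that hurt, only that pain per nodule is unchanged. That the t test could point against PIT is a possibility under assumed selective prevention, not something the documents predict. The chi-squared test has the same defect only if its denominator is nodule patients, which the article leaves open.

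This should be corrected before analysis. It bears on a secondary endpoint, though one tied to the trial's second stated purpose.

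**What to change.** - **Main between-arm comparison.** The proportion of all randomised patients, by allocated arm, with a painful nodule by 6 months: a nodule plus the protocol's own 20% VAS rise. Patients without a nodule count as non-events. State this denominator for the chi-squared test.
- **Death before 6 months.** State the handling in advance, since 25% are expected to die by then. One option is to count death without a painful nodule as a non-event and add a sensitivity analysis with death as a competing event.
- **Nodule patients.** Report change in pain as a within-patient description, with no between-arm p-value. This still answers whether nodules are symptomatic.
- **Supportive analysis.** Intervention-site VAS in all randomised patients, measured from the randomisation baseline. It also captures pain from the procedure and from radiation skin effects, so it is not the named endpoint, and a nodule effect on mean VAS will be heavily diluted.

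The cost is wording and some extra analysis; the VAS is already collected from everyone. The drawback is modest power, because the effect is spread over many patients without nodules: about 40% to 76% under the assumed range. What is gained is a comparison that randomisation supports.

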### Protocol adherence

No major problems are anticipated in terms of adherence to intervention protocols as the experimental arm only involves three fractions of standard radiotherapy delivered over approximately 5 min on three consecutive days.

### Data handling and analysis

All forms will be entered in a trial defined database for which some consistency checking will be programmed in. Data managers will check for missing and invalid data using SQL queries and statistical programs. Any queries will be highlighted on trial-specific query forms and returned to the centre for correction and/or clarification. The data will be stored on a secure server access to which is restricted to MAHSC-CTU staff. The data management procedures can be found in the PIT Data Management Manual, this is an internal document created for use by the Data Manager within the MAHSC-CTU and contains all procedures defined to ensure the data management and validation procedures are properly carried out.

